### Data and power analysis

The analyses will include a quantitative assessment of Aims 1 to 3 and an economic cost analysis. Table 1 outlines the study aims and hypotheses. The data and power analysis approaches are presented in sequence for each aim by hypothesis for the experimental comparison only, as the pooled-group analyses have inferential limitations. Power was assessed using SamplePower 3.0 [73].

#### Specific aim 1

For hypothesis 1, the program is the unit of analysis, and DDCAT (fidelity) scores represent the dependent variable and the cohort assignment (NIATx vs. wait-list) is the independent variable. A two tailed analysis of covariance (α = 0.05) with 25 programs per cohort group will compare post- implementation mean fidelity scores between groups, with pre-implementation scores as the covariate. With a correlation between pre- and post- implementation DDCAT scores equal to 0.5, this analysis has power (β = .86) to detect a large effect. Prior research concerning one-year changes in DDCAT scores suggests that we can expect a large effect [62].

#### Specific aim 2

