The date of the DDCAT assessment will serve as the index date for hypothesis 2 (Aim 2). All patients admitted to each program, 45 days before and 45 days after the DDCAT assessment date, will be extracted from the state administrative databases. The outcomes will be the proportion of program patients: 1) screened, 2) diagnosed, and 3) receiving integrated medication and psychosocial services, compared to ad hoc strategies (wait-list comparison sites). Each outcome has a value of 1 (yes) or 0 (no), and interest is in the difference in the rate of each outcome, accounting for the clustering of observations within sites. This analysis calls for a multi-level logistic regression model. The observations at each time point are independent, and therefore this is not a longitudinal (repeated measures) analysis. Instead, there are four independent groups (NIATx pre-implementation, NIATx post-implementation, wait-list pre-implementation, and wait-list post-implementation) in a 2 (group) by 2 (time) analysis, with primary interest in the group by time interaction. Due to the large number of observations, a logistic regression has power equal to 0.75 to detect a small effect (OR = 1.5; .10 difference in proportions) and power of 1.0 to detect a medium effect (OR = 2.33; .20 difference in proportions). These power estimates are based on standard logistic regression. We will apply a correction to the standard errors to adjust for the interclass correlation at the site level in order to avoid Type I errors due to the dependence of the clustered observations [74].

#### Specific aim 3

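### Aim 2 tests a free group-by-time interaction; adjusting for a pre-notification program baseline would be more precise, by a variance cut of (1−r)/2 with r not given for Aim 2

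*Protocol article*

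**What the plan says.** Under Specific aim 2 in the section Data and power analysis, each outcome is binary and the patients differ between periods: "The observations at each time point are independent, and therefore this is not a longitudinal (repeated measures) analysis". The protocol then states "This analysis calls for a multi-level logistic regression model", with four cells (two arms, before and after) analysed "in a 2 (group) by 2 (time) analysis, with primary interest in the group by time interaction". Both arms' baseline rates are therefore left free.

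Under Specific aim 1, the same randomised programs are handled differently. The analysis of covariance "will compare post- implementation mean fidelity scores between groups, with pre-implementation scores as the covariate".

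Two timing statements matter. The section Randomization says that programs learn their assignment, and Cohort 1 its coach, after the baseline DDCAT assessment. Specific aim 2 draws its patients from a window of 45 days on each side of that assessment.

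On power, Specific aim 2 gives 0.75 for an odds ratio of 1.5 and adds "These power estimates are based on standard logistic regression". It states no patient count, intraclass correlation (ICC) or pre-post correlation. The only pre-post correlation in the article is 0.5, for DDCAT scores under Specific aim 1.

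**The concern.** Before programs know their assignment, any difference between the arms in screening, diagnosis or service rates is chance. The interaction takes the post-period difference and subtracts the whole observed baseline difference, noise included. An adjusted analysis subtracts only the part that predicts the post-period rate. The protocol does this for Aim 1 and gives no reason for not doing so for Aim 2.

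At stake is precision. The abstract lists penetration as a primary outcome measure. Its stated power for a small effect is 0.75 before any allowance for clustering. The number of programs is limited to about 50 (49 randomised, according to Trial status), so the choice of analysis is one of the few ways left to gain precision.

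**Working it through.** **The plan's own figure.** The power of 0.75 cannot be reproduced because the number of patients is not given. It can only be back-solved. Both stated effects fit a reference rate of 0.50: (0.6/0.4)/(0.5/0.5) = 1.5 and (0.7/0.3)/(0.5/0.5) = 2.33.

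- As a simple two-group comparison, 0.75 needs about 343 patients per group, or 343/25 ≈ 14 per program.
- As a test of the interaction, the variance of the log odds ratio contrast is (4 + 4 + 4 + 4.17)/n = 16.17/n. At n = 690 per cell the standard error is 0.153, ln(1.5)/0.153 = 2.65, and power is Φ(2.65 − 1.96) ≈ 0.75. That is 690/25 ≈ 28 patients per program and period.

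The article does not say which was meant. With 345 per cell, the interaction would have power of only about 0.47, even without clustering.

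**General gain.** Let s² be the variance of a program's observed rate in one period, equal before and after, and r the pre-post correlation of those rates.

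- Interaction (difference in change): variance proportional to 2s²(1−r).
- Adjusted for baseline: proportional to s²(1−r²).
- Ratio: (1−r²)/[2(1−r)] = (1+r)/2, so the cut is (1−r)/2.

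| r | cut in variance |
|---|---|
| 0.3 | 35% |
| 0.5 (the DDCAT value) | 25% |
| 0.7 | 15% |
| 0.9 | 5% |

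Estimating the slope with 50 programs inflates the adjusted variance by about 1 + 1/46. At r = 0.5 the ratio becomes 0.75 × 1.022 = 0.766, a cut of about 23%.

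**What r could be.** For m patients per program and period, r = m·ICC·CAC/[1 + (m−1)·ICC], where CAC is the correlation of site effects between periods. Assumed ranges of m from 14 to 100, ICC from 0.01 to 0.20 and CAC from 0.6 to 0.95 give cuts from about 4% to about 46%.

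**Illustration (all inputs assumed).** Take ICC 0.05, CAC 0.8, 28 post-period patients per program, and 14 baseline patients, which is half of 28 because half the window is dropped. Variances are per program, in units of p(1−p).

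- Variance of a rate, m = 28: (1 + 27 × 0.05)/28 = 0.0839.
- Variance of a rate, m = 14: (1 + 13 × 0.05)/14 = 0.1179.
- Covariance between periods: 0.05 × 0.8 = 0.04.
- Interaction on the full window (28 and 28): 2 × (0.0839 − 0.04) = 0.0879.
- Adjusted on the restricted window (14 and 28): 0.0839 − 0.04²/0.1179 = 0.0704.
- Ratio: 0.0704/0.0879 = 0.80, a cut of about 20%.

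For power, 0.75 corresponds to a noncentrality of 1.96 + 0.6745 = 2.6345. Clustering inflates the interaction's variance by 28 × (0.0839 − 0.04) = 1.23, giving 2.6345/√1.23 = 2.376 and power Φ(0.416) ≈ 0.66. After adjustment, 2.376/√0.80 = 2.66 and power is Φ(0.70) ≈ 0.76. With t critical values the pair is about 0.64 and 0.74.

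**Simulation.** With 25 + 25 programs and binary outcomes, adjusting at site level cut the variance by 34% (m = 14) and 23% (m = 50) at ICC 0.05 and CAC 0.8. Both estimators gave the same mean effect. At m = 28 in both periods, type I error was 5.1% for both.

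**Effect of the window.** If a share c of the effect already shows in the baseline, the interaction is biased by about −c times the effect and the adjusted estimate by about −r·c times it. With c = 0.25, a true difference of 0.10 and r ≈ 0.48 (m = 28 in both periods), the expected estimates are 0.10 × (1 − 0.25) = 0.075 and 0.10 × (1 − 0.48 × 0.25) = 0.088.

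**The case against.** The best defence is that the interaction is a legitimate analysis of a randomised pre/post cluster design. Nothing in the quoted sentence is wrong, and the simulated mean effects agree. That stands. A reader might infer that the test is biased or contradicts Aim 1, and the document does not support this.

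A reader might also take the whole Aim 2 baseline to precede assignment. That holds for the DDCAT score. Up to half of the Aim 2 window may follow notification, so equal baseline rates are assured only for admissions before it. This does not favour the interaction, which the working shows is hurt more by such leakage, but it does mean the window must be changed.

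Aim 1's method cannot simply be copied, because there is no patient-level baseline. The covariate must be a noisy program rate, or the model must carry a common-baseline constraint. The type I error shown is for the site-level analysis only; none was computed for the constrained logistic model.

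Finally, a reader might take 15–35% as a property of this trial and free of charge. It restates r = 0.7 to 0.3, which the document does not give for Aim 2. The 28 patients per program and period come from one of two readings of the 0.75. Keeping 28 baseline patients would give a ratio of 0.74 and power of 0.79, but the remedy's own window does not allow that.

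**Conclusion.** The point holds as one of efficiency: a cheap improvement. The primary Aim 2 test is valid, but it gives up precision that a randomised design with a program-level baseline already provides. In large samples with a clean baseline, adjustment is never less efficient. How much is gained depends on r for the Aim 2 outcomes, which is unknown: the DDCAT value of 0.5 is only a guide, and high program-level stability would leave little to gain. In the illustration, the restricted window reduces the gain but does not remove it. Those power figures also assume that the stated 0.75 refers to the interaction before clustering.

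**What to change.** - Make the post-implementation group effect the primary Aim 2 estimate. Either adjust for the program's own baseline rate, or fit the multi-level logistic model to both periods with a common baseline for the two arms (no group term at baseline).
- Account for clustering by site and by site within period.
- Define the Aim 2 baseline as admissions before the program is notified of its assignment.
- Keep the group-by-time interaction as a sensitivity analysis.
- If the common-baseline logistic model is chosen, check its type I error by simulation with about 50 programs.

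The cost is a change to the analysis text and to which admissions count as baseline, one degree of freedom for the covariate (about 2 points of the gain), and fewer baseline patients, perhaps half if notification promptly follows the assessment. No new data are needed.

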## NIATx implementation strategy

The NIATx implementation strategies will be incorporated into this conceptual model (see Step 4 in Fig. 1) to determine the effectiveness of NIATx in implementing integrated services for persons with co-occurring substance use and mental health disorders. NIATx combines process improvement tools and techniques (e.g., consumer-centered walk-through and PDSA rapid change cycles) with quality improvement interventions such as coaching, learning sessions, and “interest circle” calls [51–53]. NIATx implementation strategies have been widely adopted and successfully utilized to improve and sustain access to care and addiction medications [54–59]. The NIATx200 study dismantled three components of the NIATx implementation strategy (learning session, coaching, and interest circle calls) or a combination of all three to determine key elements for improving wait time, admissions and retention [60]. This dismantling of NIATx found important differences by implementation strategy and outcome; however, it was in fact an “intent-to-treat” analysis [61]. Fidelity and extent of variation within each component were not assessed in the NIATx200 study.

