3	NIATx Fidelity Scale^3^	NIATx strategy fidelity and extent of and duration to complete activities (SIC)		X		
1	Program characteristics^1^	Program Size (Admissions), Program Type, ASAM Levels of Care, Payment Sources	X	X	X	X
2	Patient Characteristics	Age, Gender, Race, Ethnicity	X	X	X	X

State of Washington staff will be trained on how to conduct DDCAT and CFIR Index assessments by co-PI ([name]). Two-person teams will schedule and conduct each DDCAT assessment. Additional training or consultation will help answer questions identified at the site visits. Program characteristics are collected during the DDCAT assessments

Data will be collected by the state of Washington staff and NIATx coaches using standardized instruments for each program participating in the study

NIATx Fidelity scoring (Total and 7 subscale scores are organized by preparation, implementation and sustainment phases) will be assessed by two person teams at the end of the active implementation period for each program. Data sources will include a composite of interviews, review of walk-through results, change project forms, coach notes and sustainability plans

At the time of the study, Washington State was transitioning to Managed Care Organizations (MCOs) to pay for the delivery of substance use disorder (SUD) and mental health (MH) services. The transition involved integrating data from two systems: 1) the Treatment and Assessment Reports Generation Tool (TARGET), covering SUD clients and services; and 2) the Mental Health Consumer Information System (MH-CIS), covering community MH clients and services into a new Behavioral Health Data System (BHDS). The study will capitalize and leverage the State of Washington’s experience in utilizing standardized state-wide clinical management information databases for addiction and mental health treatment [67–70]. Implementation penetration outcomes will assess changes in the proportion of patients screened, diagnosed and receiving integrated psychosocial or medication services (Aim 2). The services data will be extracted from the BHDS as well as TARGET and MH-CIS legacy systems. It will include de-identified client level data for all patient admissions to study programs within a 45-day window before and after each DDCAT assessment date (Additional file 1). The information will be transferred to the study team using appropriate security protocols.

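### Aim 2: the stated group-by-time model has no patient-level terms, so an arm-specific change in who is admitted would count as a NIATx effect on penetration

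*Protocol article*

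**What the plan says.** **Aim 2 model (Data and power analysis, Specific aim 2).** Each outcome is a yes/no value per patient. The model is a multi-level logistic regression with observations clustered in sites, "in a 2 (group) by 2 (time) analysis, with primary interest in the group by time interaction". The section describes the pre- and post-implementation patients of the two arms as four independent groups. Patients are all admissions within 45 days either side of the DDCAT assessment date, taken from state databases. No patient characteristic is named in the model.

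**What is collected (Data collection/variables, Table 2).** A row labelled Aim 2 lists patient characteristics, "Age, Gender, Race, Ethnicity", at all four time points. A row labelled Aim 1 lists program characteristics, "Program Size (Admissions), Program Type, ASAM Levels of Care, Payment Sources".

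**When programs learn their arm (Randomization).** They are told after the baseline DDCAT assessment, so well before the post-implementation patients are admitted.

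**The other aims.** Aim 1 names one covariate: it compares post-implementation scores "with pre-implementation scores as the covariate". Aim 3 states that site characteristics related to the outcomes will be added to its regressions.

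**The concern.** Randomization acts on programs and protects the comparison of programs. It does not fix which patients arrive a year later, when every program knows its arm. Because each time point samples different people, a program's pre-to-post change in a rate mixes two things: a change in what the program does for a given kind of patient, and a change in which patients it admits. A mix change that is the same in both arms cancels in the interaction. One that differs between arms does not, and the program's own baseline rate cannot remove it.

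At stake is the interpretation of Aim 2. NIATx could be credited with, or charged for, part of a change in penetration that comes from a different patient population. The variables that would allow a partial correction are already collected for this aim.

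**Working it through.** **1. The plan's yardstick.** Specific aim 2 states power .75 for a .10 difference (OR 1.5) and 1.0 for a .20 difference (OR 2.33), from standard logistic regression. No number of patients is given, so these cannot be reproduced directly. Solving backwards, a two-group comparison of .5 with .6 needs 343 per group for power .75, and the same 343 gives .9997 for .5 with .7. The two stated powers agree with each other. The .10 difference is the yardstick below.

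**2. Size of the false effect, simple form (assumed inputs).** With no true effect, bias = (arm-specific shift in a group's share) × (gap in outcome rate between that group and the rest).
- Shift 10 points, gap 15 points: .10 × .15 = .015
- Shift 20 points, gap 20 points: .20 × .20 = .040

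These are 15% and 40% of .10.

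**3. Size, logistic form (assumed inputs).** Overall rate .40, a binary trait held by 30% of patients, no true effect, and a shift in one arm only at follow-up. Each cell shows the spurious difference, then the spurious interaction odds ratio.

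| Trait OR | 5-point shift | 10-point shift | 20-point shift |
|---|---|---|---|
| 1.5 | .005; 1.02 | .010; 1.04 | .020; 1.08 |
| 2 | .008; 1.04 | .017; 1.07 | .034; 1.15 |
| 3 | .013; 1.06 | .027; 1.12 | .053; 1.24 |

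Most of the grid lies between 0.5 and 4 points. Only the extreme corner (trait OR 3 and a 20-point shift) exceeds that.

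**4. Effect on the false-positive rate (assumed inputs).** Take 49 randomized programs (Trial status), assumed split 25/24; outcome variance pq = .25; m = 20 to 80 admissions per window; ICC .02 to .10; correlation .8 between a program's underlying rates at the two times.

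SE = sqrt{ pq × [2(ICC + (1 − ICC)/m) − 2 × .8 × ICC] × (1/25 + 1/24) }

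- ICC .02, m = 80: sqrt{.25 × [.0645 − .032] × .0817} = .0258
- ICC .10, m = 20: sqrt{.25 × [.290 − .160] × .0817} = .0515

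Two-sided rejection rate from the noncentral t with 47 df and noncentrality bias/SE, nominal .05, over the four corners of the ICC and m ranges:
- bias .005 to .010: .051 to .067
- bias .015: .059 to .088
- bias .040: .118 to .331

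The .331 needs a 20-point shift, a 20-point gap and the smallest SE together.

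**5. Does the argument carry over to Aim 1?** The plan states "A two tailed analysis of covariance (α = 0.05) with 25 programs per cohort group", a pre-post correlation of 0.5, and that "this analysis has power (β = .86) to detect a large effect". The effect has no number. With residual variance 1 − .5² = .75, an effect of d = .76 gives .860 at 25 per arm and .852 at 25/24.

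Adding three program terms (4 covariates in all, counting baseline DDCAT) also inflates the variance through expected chance imbalance, by (N − 3)/(N − 3 − k), where k counts all covariates. With N = 49:
- baseline DDCAT only (k = 1): power .845
- three more terms (k = 4) explaining 0, 5, 10 or 20% of residual variance: .818, .837, .856, .894

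Break-even: 1 − (49 − 3 − 4)/(49 − 3 − 1) = 1 − 42/45 = 6.7%, about 7%. If only degrees of freedom are charged, the same four cases give .851, .869, .886 and .919, which makes the gain look free when it is not.

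**The case against.** **An article need not list covariates.** The full protocol or analysis plan may add them. The article never says the Aim 2 model is unadjusted, and labelling the patient row in Table 2 as Aim 2 may signal intended use. This stands as a caution: one cannot infer that the final analysis will ignore these variables. But the article does specify the model's terms, and it mentions covariates in the other two aims, so the point concerns a stated model and not just an absent list.

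**The mechanism is thin.** Trial staff do not recruit or consent patients, so the usual recruitment bias of cluster trials is absent. A reader might infer from the background that NIATx is known to change who is admitted. The text does not say so: "to determine key elements for improving wait time, admissions and retention" describes the outcomes of an earlier study, and nothing there concerns patient mix. This stands. An arm-specific shift is possible but not documented.

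**Demographics are a weak handle.** A shift toward patients with more severe or co-occurring illness would be only partly captured by age, gender, race and ethnicity. Adjustment also changes the odds ratio being estimated. The first part stands as a limit on the fix. Reporting standardized rates meets the second.

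**H2 concerns the proportion of program patients.** Standardizing sets aside who is admitted and so asks a slightly different question. That is a reason to show both results.

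**A reader might extend the point to Aim 1** and call the unused program characteristics lost precision. The documents do not support that. They give no figure for what these characteristics explain beyond baseline DDCAT, and below about 7% of residual variance three extra terms lose power.

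**Conclusion.** The point holds for Aim 2 only. As stated, the model attributes any arm-specific change in patient mix to NIATx, although four relevant patient variables are collected for that aim. The false effect is about 0.5 to 4 points against the planned .10 under most of the assumed inputs, and more only if a large shift meets a strongly prognostic trait. Every input to that range (shift, outcome gap, ICC, admissions per window, correlation over time) is an assumption. A bias of 1 point or less barely moves the false-positive rate. The figure of about one in three is a worst corner and should not be read as expected. This is a modest but cheap improvement, not a demonstrated bias. Aim 1 needs no change on this ground.

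**What to change.** In Specific aim 2, state that each model includes age, gender, race and ethnicity as patient-level fixed effects, besides group, time, their interaction and site clustering. Report the group-by-time contrast as a difference in rates standardized to the pooled patient mix, so that the change in the conditional odds ratio does not matter. Give the unadjusted model alongside as a sensitivity analysis. Leave the Aim 1 analysis of covariance as it is.

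Cost: wording and slightly more analysis, with no new data. Limit: it removes only the part of a case-mix shift that these four variables capture, and the report should say so.

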## Background

Access to integrated treatment services for individuals with co-occurring substance use and mental health disorders is a longstanding problem in behavioral health care [1, 2]. The provision of integrated mental health and substance use services during the same treatment episode by the same clinical provider addresses national policy statements and expert consensus guidelines underscoring the benefits of integrated treatment [1–3]. It is also preferred by patients and families [4]. However, a significant gap remains between the availability of “one-stop” integrated services and the actual receipt of integrated services for individuals with co-occurring disorders. Despite increased awareness, adequate integrated treatment for individuals with co-occurring substance use and mental health disorders occurs infrequently [5, 6]. In the United States, only 18% of specialty addiction programs and 9% of mental health programs offer integrated services [7]. Availability of integrated services is not associated with receipt of services. Consumers with co-occurring disorders report only receiving integrated services between 7 to 9% of the time [8, 9]. However, it is unclear if these individuals had their co-occurring disorders addressed in treatment at the same time or if they even received integrated services.

The current system represents an undesired but chronic, systemic artifact for policymakers and treatment providers, and even more so for families and individuals suffering from co-occurring disorders [6, 10–12]. The resulting fragmented system of care requires multiple provider interactions and integrated care is almost non-existent. The disease burden associated with co-occurring disorders represents a substantial public health concern [13–20]. Inadequate access to effective integrated treatment results in poorer public health and societal outcomes [21–25]. The impact on the United States healthcare system is significant. By 2020, annual expenditures in the US for co-occurring substance use and mental health disorders are projected to reach $281 billion [26].

Despite these facts, integrated services for individuals with co-occurring disorders are not being widely implemented in behavioral health organizations [27, 28]. Research on effective implementation of evidence-based approaches to integrated treatment for co-occurring disorders is sorely needed [29–31]. This research study addresses this gap utilizing an implementation science approach.

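### The Aim 2 power of 0.75 for a small effect assumes independent patients, so it is effectively an upper figure for the planned clustered group-by-time test

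*Protocol article*

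**What the plan says.** The Abstract of the protocol article lists penetration as a primary outcome, next to DDCAT fidelity. Under Data and power analysis, Specific aim 2, each penetration outcome is a yes/no variable per patient. Patients are those admitted within 45 days either side of the DDCAT date. On the model the article says: "This analysis calls for a multi-level logistic regression model". The design is two groups by two times, "with primary interest in the group by time interaction".

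Power is then stated, and the only reason offered is that there are many patients. For an odds ratio of 1.5 the text reads "a logistic regression has power equal to 0.75 to detect a small effect (OR = 1.5; .10 difference in proportions". For an odds ratio of 2.33 it gives a power of 1.0, tied to a .20 difference. The article then names the basis of both figures: "These power estimates are based on standard logistic regression". Clustering enters only afterwards, as a step in the analysis: "We will apply a correction to the standard errors to adjust for the interclass correlation at the site level". The purpose given for that step is protection against Type I error.

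The section gives no total number of patients, admissions per program, ICC, design effect, correlation between a program's pre and post rates, or base rate for any outcome.

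**The concern.** The stated power belongs to an analysis of independent patients, and the trial will not run that analysis. Programs are randomized, and patients within a program resemble each other. The correction that the article promises widens the standard errors. This keeps the false-positive rate honest, but power falls unless something else offsets it. Here the only offset is the stability of each program's own rate from pre to post, which the article does not discuss.

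At stake is how an Aim 2 result is read. The unclustered 0.75 is already below the customary 0.80, so there is no margin to absorb clustering. A reader who takes 0.75 at face value would give a non-significant small effect more weight than the design may support.

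**Working it through.** **Inputs.** From the article: power 0.75 at OR 1.5 and 1.0 at OR 2.33; 25 programs per arm (Specific aim 1); the group-by-time interaction as target. Assumed: two-sided α = 0.05 (stated for Aim 1, not repeated for Aim 2); ICC of .01, .05 and .10; cluster autocorrelation (CAC, the pre-post correlation of program effects) of 0, 0.5, 0.8 and 1.

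**Step 1: base rate implied by the effect sizes.** OR(p, p+d) = [(p+d)/(1−p−d)] / [p/(1−p)].

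| p | OR for d = .10 | OR for d = .20 |
|---|---|---|
| .30 | 1.556 | 2.333 |
| .40 | 1.500 | 2.250 |
| .50 | 1.500 | 2.333 |

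Only a 50% reference rate reproduces both stated pairs.

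**Step 2: recover the plan's figures.** Without N they cannot be reproduced forwards, so N is back-solved.

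- Two-group comparison, .50 vs .60, power 0.75: 343 per arm. The same 343 gives 0.9997 for .50 vs .70. The two stated figures therefore agree with each other when clustering is ignored.
- Interaction, four cells with rates near .5: n per cell = 16 × [(1.960 + 0.674)/ln 1.5]² = 16 × (2.634/0.4055)² ≈ 675, and 675/25 = 27 patients per program and period. Using .6 in the one changed cell gives 683 instead, which makes no practical difference.

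**Step 3: small-effect power with clustering, interaction reading.** Design effect DE = 1 + (m−1)·ICC − m·ICC·CAC with m = 27, and power = Φ(2.634/√DE − 1.96). This is the usual approximation, applied on the log-odds scale.

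| CAC | ICC .01: DE, power | ICC .05: DE, power | ICC .10: DE, power |
|---|---|---|---|
| 0.8 | 1.04, 0.73 | 1.22, 0.66 | 1.44, 0.59 |
| 0.5 | 1.13, 0.70 | 1.63, 0.54 | 2.25, 0.42 |
| 0 | 1.26, 0.65 | 2.30, 0.41 | 3.60, 0.28 |

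DE equals 1 when m·(1−CAC) = 1, that is CAC = 1 − 1/27 = 0.963, whatever the ICC. Only at or above that value is 0.75 kept. At CAC = 1 power is about 0.75 to 0.79 over the same ICCs.

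**Step 4: small-effect power if 0.75 was meant for two groups.** With m = 343/25 = 13.7 and DE = 1 + (m−1)·ICC = 1.13, 1.64 and 2.27, power is 0.70, 0.54 and 0.42.

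**Step 5: medium effect, interaction reading.** With cell rates .5, .5, .5 and .7, SE² = (3/.25 + 1/.21)/675 = 0.0248, SE = 0.158 and z = 0.847/0.158 ≈ 5.38. Power is Φ(5.38/√DE − 1.96). At ICC .05 it is 0.94 for CAC 0 and about 0.99 or more for CAC 0.5 and above. At ICC .10 it is 0.81, 0.95 and 0.99 for CAC 0, 0.5 and 0.8.

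**The case against.** Several points count for the plan, and most of them stand in part.

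- **The basis is disclosed.** The article says openly that the figures come from standard logistic regression, and the two figures agree with each other. This is not a hidden assumption or an arithmetic slip. Disclosure does not supply the missing figure, however: no cluster-adjusted power is given for a primary outcome.
- **The planned test is not invalidated.** The analysis is multi-level with corrected standard errors, so the Type I error is addressed. The point concerns power only.
- **The same programs are measured twice.** The pre-post contrast removes stable program differences, so the CAC 0 row is the pessimistic end. With CAC 0.8 and ICC .01 the loss is only 0.02. This is why the CAC 0.8 row comes first.
- **A reader might infer that both figures fail.** The calculations do not support this. The medium-effect power stays at 0.94 or more up to ICC .05.
- **A reader might infer that a low base rate makes matters worse**, since the Background says "Consumers with co-occurring disorders report only receiving integrated services between 7 to 9% of the time". The documents do not support this either. That figure is consumer-reported national background, and the article itself doubts what it measures. It is not a rate for all patients admitted to the study programs, and it says nothing on screening or diagnosis. The direction also depends on how the effect is held. At 8% with 675 per cell and no clustering, OR 1.5 gives power of about 0.32, but a fixed .10 difference (OR 2.52) gives 0.94, above the stated 0.75. What remains is narrower: away from 50%, the odds ratio and the difference are no longer the same target.

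**Conclusion.** The point holds for the small-effect figure. For the analysis the article plans, 0.75 is effectively an upper figure, kept only if program effects are almost perfectly stable from pre to post (CAC of about 0.96 or more on the back-solved numbers). Over ICC .01 to .10, small-effect power runs from 0.73 down to 0.59 with CAC 0.8, from 0.70 to 0.42 with CAC 0.5, and from 0.65 to 0.28 with CAC 0. The two-group reading gives 0.70 to 0.42.

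The medium-effect power of 1.0 is slightly optimistic but largely sound: 0.94 or more up to ICC .05, and 0.81 to 0.99 at ICC .10 for CAC 0 to 0.8.

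The size of the loss rests on assumed values of ICC and CAC, on a back-solved N, on a 50% base rate inferred from the effect-size pairs, and on two-sided α of 0.05. The article settles none of these for Aim 2. That the true power is far below 0.75 is therefore possible but not shown. What is shown is that the stated figure does not describe the planned test.

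**What to change.** In Specific aim 2, replace 0.75 and 1.0 with cluster-adjusted power for the group-by-time test, or with the minimum detectable effect at 80% power. State the inputs:

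- the 49 programs randomized (Trial status);
- the expected admissions per program in each 90-day window;
- the program-level ICC and the between-period correlation, which can be estimated from the legacy TARGET and MH-CIS data the study already draws on;
- a base rate for each outcome (screened, diagnosed, receiving services), with the target effect fixed either as an odds ratio or as a difference, because the stated pairs match only at 50%.

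If the ICC and between-period correlation cannot be estimated in time, give power over a stated range of both.

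The cost is a recalculation and a less favourable stated power for the small effect. The design, the analysis model and the number of programs stay as they are.
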